## Abstract

**Background:**

More than one in six women will be sexually assaulted in their lifetimes, most by men they know. The situation on university campuses is even more startling, with as many as 1 in 4 female students being victims of rape or attempted rape. The associated physical and mental health effects are extensive and the social and economic costs are staggering. The aim of this randomized controlled trial is to determine whether a novel, small-group sexual assault resistance education program can reduce the incidence of sexual assault among university-attending women, when compared to current university practice of providing informational brochures.

**Methods/Design:**

The trial will evaluate a theoretically and empirically sound four-unit, 12-hour education program that has been demonstrated in pilot studies to have short-term efficacy. Three of the four units provide information, skills, and practice aimed at decreasing the time needed for women to assess situations with elevated risk of acquaintance sexual assault as dangerous and to take action, reducing emotional obstacles to taking action, and increasing the use of the most effective methods of verbal and physical self-defense. The fourth unit focuses on facilitating a stronger positive sexuality from which women may resist sexual coercion by male intimates more successfully. The trial will extend the pilot evaluations by expanding the participant pool and examining the long term efficacy of the program. A total of 1716 first-year female students (age 17 to 24 years) from three Canadian universities will be enrolled. The primary outcome is completed sexual assault, measured by *The Sexual Experiences Survey - Short Form Victimization* instrument. Secondary outcomes include changes in knowledge, attitudes, and skills related to the process of sexual assault resistance. Outcomes will be measured at baseline, 1 week, 6, 12, 18, and 24 months.

**Discussion:**

The results of the trial will be used to produce a maximally effective sexual assault resistance education program that can be adopted by universities, to assess whether aspects of the program need to be strengthened, and also to indicate how long the effects of the program last and at which point in time refresher sessions may be necessary.

**Trial registration:**

ClinicalTrials.gov NCT01338428

## Background

### Epidemiology and impact

By conservative estimates, between 18 and 25 percent of women will experience rape or attempted rape in their lifetimes (i.e., experience sexual penetration by the use of threats, force or drugging) [1-3]. If sexual assault not including penetration (i.e., forced, threatened or drugged non-consensual sexual touching) and sexual coercion (i.e., using tactics other than physical force or threats, such as “continual arguments and pressure”) are included, the percentage increases dramatically [4-6]. The incidence of sexual assault and coercion on Canadian and American university campuses are even more startling [6-8]. As many as 1 in 4 female students are estimated to be victims of rape or attempted rape during the relatively short time they are enrolled in post-secondary education [8]. First year students are most at risk [9], probably because university entrance is a transition time for adult intellectual, social, and sexual development, both healthy and unhealthy.

The physical and mental health effects of rape and other forms of sexual coercion have both acute and chronic negative consequences for victims, as well as extensive social and economic consequences. Physical consequences include unwanted pregnancies and sexually transmitted diseases, including HIV and Hepatitis C, [10], cigarette smoking, and alcohol and drug consumption [11,12]. Short and long-term psychological consequences include depression, post-traumatic stress disorder, suicidal ideation, lack of sexual enjoyment, and fear [13-15]. In Canada alone, sexual assault and other forms of violence against women cost at least $1.5 billion each year in health-related expenses [16] and substantially more in social services, legal processes, and lost time from employment [17]. Fear of rape also affects the quality of life of a high proportion of women who are not rape victims [18-20]. This fear is connected to precautionary strategies that restrict women’s movements at certain times and in certain spaces [21-23], and consequently limits women’s employment and recreational opportunities [20,22].

Girls and women between the ages of 14 and 24, regardless of their sexual orientation, are most at risk of being sexually assaulted by a man [1,3,24-26]. It, therefore, makes sense that efforts to protect women from sexual assault should take place prior to, or within, this ten-year time window. Although many sexual assaults occur prior to age 18 [27,28], restrictions on the types of sexual content that can be presented in schools make them a difficult site for implementing and evaluating rape prevention programs. In contrast, university campuses are ideal environments as students are adults, and therefore the restrictions are fewer.

### Rape prevention efforts on university campuses

There has been a long history of educational efforts to attempt to prevent rape on and off campus [29,30]. Historically, the most common approach on university campuses, due in large part to structural practicalities, has been to present coeducational audiences with correct information about rape (e.g., most rapes are committed by male acquaintances, undermining rape myths such as that women ‘provoke’ rape if they wear revealing clothes, etc.). These “universal” approaches try to reach both men and women but are not tailored for either [31] and have been shown to result in temporary improvement in rape knowledge and attitudes at best [32-35]. Moreover, most of these programs do not measure incidence or severity of sexual assaults (perpetration or victimization) following the program. In Canada, at the time the present trial began, universities’ rape prevention education appeared to range from provision of brochures to a five minute section of a play done for student orientation (e.g., *Single & Sexy*, University of Windsor) to 60–90 minute workshops for students (e.g., Queen’s University) unaccompanied by evaluation research.

The authors of most reviews of rape prevention efforts conclude that theoretically-based programs targeted at single-sex audiences have more promise than mixed-sex programs [29,31,34,35]. The exception to this recommendation is seen in more recent educational efforts, where men and women in the audience are being approached as potential bystanders to situations that are developing rather than as perpetrators or victims [36-38]. Even in these circumstances, the same programming is normally offered to men and women in single-sex groups. Educating men to reduce their perpetration is a necessary goal but one that has so far been met with very limited success [39,40]. Until such time as there is widespread social change or better programming for men, effective rape resistance education (also known as risk reduction programs) for female students is the most promising option [41].

### Research on rape resistance education programs and guiding frameworks

Within the past fifteen years, a consensus view of the necessary elements of rape resistance education has emerged. Comprehensive critical reviews [29,35] stress the importance of the process of education and claim that effective rape prevention programs are likely to be those that actively involve participants and create a sense of high personal relevance. Building on social psychological theories of attitude change and persuasion, such as Eagly and Chaiken’s attitude change model [42,43], recommendations for program design include the use of expert status and positive consensus information to address cognitive, emotional, and behavioural aspects of attitude processes while ensuring personal motivation and decreased distractions and negative emotional states.

In 1996, Nurius and Norris [44] “offer[ed] a theoretical model that consolidates background, environmental, and intrapersonal variables related to women’s experience of sexual coercion in dating into a coherent ecological framework and present[ed] for the first time a cognitive analysis of the processes women use to formulate responses to sexual coercion” (p. 117). A key article synthesizing a decade of research on rape [41] based its recommendations for rape resistance education programs largely on the Nurius and Norris model expanding it with self-defence training based on research examining tactics predicting successful resistance, [45]. This program plan, named by them “AAA: Assess, Acknowledge, and Act”, expands on the cognitive appraisal model.

### Previous trials of rape resistance programs

A systematic review of the literature confirms that despite the size of the ‘at risk’ population and the seriousness of health impacts of rape and sexual assault, a rigorous randomized controlled trial (RCT) of a rape resistance education program has not been conducted. Among the published studies of programs for female university students, only three have demonstrated a positive impact on completed rape rates. However, they have mixed effectiveness and lack the detail to allow a full evaluation of the processes and practices [46,47].

In their study, Hanson and Gidycz [48] found lower completed rape rates for women in the subsequent two months, but the benefit was only for women who had not been sexually victimized previously. This benefit for non-victimized women was not replicated in a later study that attempted to strengthen the program [49]. Increasing the focus on cognitive and emotional obstacles to resistance also did not improve the outcomes [50]. In an expanded 3-hour program with an increased emphasis on personal relevance to participants and changes expected to enhance processing of information, Gidycz et al. [51] reported a delayed benefit (occurring between 2 and 6 months following the program) for some women only. Women who took the program, and who were sexually assaulted but not raped in the two months after the program, were less likely to be assaulted in the next 4 months than were any other group of women. Gidycz et al. [46] expanded their program to two sessions and added a booster session at 3 months. The 7-hour program included a greater focus on problem solving related to reducing risk and self-defence training but was unable to produce any change in sexual assault outcomes. Orchowski et al.’s [47] addition of self-defence training was successful in producing short term (2 month) reductions in completion of sexual assault for women with and without a sexual assault history. Effects were not maintained 4 months later even with a booster session. Yeater et al. [52] tested the efficacy of reading a “skills-based” self-help book against a wait-list control with 110 college women and demonstrated a number of positive outcomes but no reduction in sexual assaults.

The few other RCTs that also emerged were evaluations of treatment or prevention programs for sexual assault survivors. For example, an RCT of the effectiveness of a self-defence program for female veterans with PTSD following sexual trauma was conducted, but only a discussion of ethical concerns related to the project was found in the published literature [53].

### Development and pilot testing of a sexuality-enhanced AAA sexual assault resistance program

Based upon the models of Nurius and Norris [44] and Rozee and Koss [41], a three-session AAA sexual assault resistance program was developed by the principal investigator of the present trial and pilot tested in the fall of 2005 and winter of 2006 on a total of 34 female students against a quasi-experimental control [54]. Positive outcomes at 1 week for women in the intervention compared to controls included increases in the perception of risk, increased self-defence self-efficacy, and higher generation of effective self-defence strategies in hypothetical sexual assault and coercion situations; negative beliefs relating to rape myths and victim provocation in sexual assault were reduced. An unplanned 3-month follow-up with approximately 50% of participants revealed that 21% of women who took the program versus 39% of controls became victims of sexual coercion or assault. Based upon these results, a revised AAA program was conceived to include additional self-defence scenarios and practice.

Rape resistance programs alone may not be enough to protect women from sexual assault in the longer term. Normative sexual practices which put men’s (presumed) sexual needs ahead of women’s have also been implicated in acquaintance sexual assault [55]. For an education program to have long-term effectiveness, it is important to integrate what women know about rape and sexual coercion into the development of their healthy sexuality and relationship practices. The Our Whole Lives (OWL) Curriculum [56], was designed: “to advance communication about sexuality and help participants address their own needs … ; to promote safer sexual practices; to build understanding of healthy sexual relationships and activities; … [and] to help participants accept, understand, and affirm their own sexuality…(p. xi)” Because these principles lay the groundwork for a positive sexuality from which unwanted sex may be resisted more successfully, an adaptation of some of the OWL curriculum units was included in a sexuality-enhanced version of the AAA program.

### Aims

#### Primary

To test the hypothesis that a novel, four-session, small-group sexual assault resistance education program can reduce the one-year incidence of sexual assault by 30% (absolute difference of 7.5%) among first-year female university students, when compared to current university practice.

#### Secondary

To test the hypotheses that the intervention can: (a) increase women’s perception of their risk of sexual assault by male acquaintances; (b) increase women’s belief that they could defend themselves if confronted with a sexual assault situation; (c) increase women’s knowledge of the most effective self-defense strategies; (d) increase women’s ability to detect risk in hypothetical situations; (e) reduce women’s rape beliefs and attitudes that impair recovery from sexual assault.

#### Tertiary

To test the hypothesis that the intervention can: (a) reduce the one-year incidence of forced sexual contact and sexual coercion; (b) maintain the improvements in the primary and secondary aims for up to 24 months.

## Methods/Design

### Study design

This is a multicentre randomized controlled trial. By necessity, the design will be open-label, whereby the participants will be aware of the nature of the assigned sexual assault intervention. There is no evidence from our pilot testing that knowledge of the assignment influences participants’ responses on key outcomes in any way. For example, post-randomization pre-intervention scores did not differ between participants who were assigned to the AAA education programs and those assigned to no-program.

### Inclusion and exclusion criteria

Inclusion criteria: (a) female subjects; (b) age 17 to 24 years; (c) first-year university student (completed no more than 10 university courses); (d) able to attend one of four scheduled programs in the semester they are enrolled; (e) provide informed consent. There are no exclusion criteria. Universities require that all attending foreign students have English proficiency; therefore all students will have sufficient English to participate.

### Recruitment

Women will be recruited from each of three sites over a 2-year period, Universities of Windsor, Guelph, and Calgary. The universities are in large and small cities, attract different demographics of students and have very different first year cultures. For example, the University of Windsor is in one of the most ethnically diverse cities in Canada, at the University of Guelph almost all first-year students live on campus, and at the University of Calgary less than 10% of first-year students live on campus. We expect total recruitment from all three sites of more than 200 each fall and winter academic term from contacted students and 50 from orientation activities or first year classes. Our pilot testing indicated that the projected rates of recruitment are achievable. When women were contacted in our pilot study, no more than 11% of them declined and this was primarily due to time considerations rather than topic.

Although recruitment will be site-specific, the information provided to participants in advertisements and in contact with the recruiters will be standardized. Recruitment will begin each year in September with e-mail contact of first year female students by the Registrar, Faculty, or Director of Student Residence. The e-mail will consist of a brief description of the study and the incentives offered and will ask those interested to contact the research assistants by telephone or e-mail. Lists of eligible women in Psychology Participant Pools will also be obtained and research assistants will contact these women. Other advertising will be done by posters in female residence halls and in women’s washrooms on campus, on electronic and physical research posting boards, and flyers left in residence mailboxes. Also, face-to-face recruitment will take place in large first-year classes, at tables in student centres and at orientation and other events.

All interested students will be asked to contact a research assistant who would explain the study in detail prior to scheduling the baseline session. Women will be screened by telephone whenever possible. In instances where women cannot be contacted by telephone they will be provided a detailed description of the study and eligibility criteria by e-mail. All prospective participants will be contacted within the early part of the fall and winter terms. Those who agree to participate will be invited to attend an in-person baseline assessment matching their chosen intervention schedule.

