#### Training of facilitators and research assistants conducting interventions

A detailed manual has been written that provides instructions for the enhanced AAA sexual assault resistance program facilitators, including session materials, scripts, and trouble-shooting advice. The Principal Investigator will conduct a joint training program for all site facilitators in late summer in the intervention years of the trial. Training will include attendance at a WenDo Women’s Self-defense two-day Basic program and another day of specialized training by a certified WenDo instructor. Research Assistants will be trained by the Principal Investigator and the Trial Project Manager in site visits in September in both intervention years.

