### Sample size considerations

The primary outcome is completed sexual assault (rape). Our 2006–2007 pilot randomized controlled trial of 214 students yielded the following cumulative incidences. For women in the control arm, the 3- and 6-month rates were 12% and 20%, respectively. For those in the sexual assault resistance education program, they were 6% and 11%, respectively. These figures correspond to a 50% relative risk reduction. This is comparable to the one previous study conducted by Hanson and Gidycz [49], which yielded a rate of 14% of rapes in their control arm and 6% in their intervention arm over a 3-month period, among women with no history of previous victimization. Given that the incremental incidence of sexual assault declines over time we estimate, for the purpose of sample size calculations, the 1-year rates to be 25% in the brochure arm and 17.5% in the educational program arm; a more conservative 30% relative risk reduction. Therefore, a sample size of 932 women (466 per group) will have 80% power to detect an absolute difference of 7.5% (25% versus 17.5% equals a 30% relative reduction) at a two-sided 5% level of significance. This is a meaningful reduction because it implies that for every 14 women who enroll in the program, 1 additional rape could be averted. Aside from power considerations, it is important to note that a sample of this size will yield a significantly positive trial when the observed difference between groups is as small as 5.4% (21.6% relative risk reduction). Although the intracluster correlation was calculated as −0.02 from our pilot study, +0.02 will be used to inflate the sample size with a design effect of 1.38 and a cluster size of 20 women. Assuming a lost-to-follow-up of 10% in the first year and 15% in the second year of follow-up, the total size of the trial will be 1716 women (932×1.38÷0.75).

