### Trial status

The first participant was randomized on September 28, 2011. Currently, 918 women have been enrolled into the on-going trial.

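### The recruitment forecast (a floor of about 1,000 women over four terms) does not support the 1,716 women on which the stated 80% power rests

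*Protocol article*

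**What the plan says.** All references are to the protocol article.

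- **Recruitment, duration:** "Women will be recruited from each of three sites over a 2-year period". The section on training of facilitators and research assistants also speaks of two years of delivery: "in site visits in September in both intervention years".
- **Recruitment, yield:** "We expect total recruitment from all three sites of more than 200 each fall and winter academic term from contacted students and 50" (these last being women met at orientation events or in class). The section adds: "Our pilot testing indicated that the projected rates of recruitment are achievable".
- **Sample size considerations:** "a sample size of 932 women (466 per group) will have 80% power to detect an absolute difference of 7.5" percentage points. After a design effect of 1.38 and division by 0.75 for losses, "the total size of the trial will be 1716 women". The Abstract repeats 1,716.
- **Lost to follow up:** the primary outcome is at 1 year, with 10% loss expected by then and up to a further 15% by the end of year 2.

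**The concern.** The article prints a target and a forecast that differ by about 700 women, and it claims feasibility for the lower one. The 80% power, the 7.5-point difference and the statement that an observed 5.4-point difference would be significant all assume an effective sample of 932 women after clustering and losses. A recruitment plan that aims only at its own forecast would not provide that. If enrolment stopped near the forecast, the chance of missing the planned effect would be about one in three under the planned design effect, and a reader relying on the stated 80% could take too much from a non-significant result.

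**Working it through.** **Inputs.** 1-year rates: "the 1-year rates to be 25% in the brochure arm and 17.5% in the educational program arm". Two-sided 5% test and 1:1 allocation. ICC 0.02 and cluster size 20. Loss 10% at 1 year; the plan's total uses 25%.

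**Formula.** With n women per arm after adjustment, n = N × (1 − loss) ÷ design effect ÷ 2, and

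power = Φ{ [|p1 − p2| − 1.96 √(2p̄(1 − p̄)/n)] ÷ √([p1(1 − p1) + p2(1 − p2)]/n) }, where p̄ = (p1 + p2)/2 = 0.2125.

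**The plan's figures reproduce.**
- n = 466: (0.075 − 0.0525) ÷ 0.0267 = 0.84, so power is 80.0%.
- Design effect: 1 + 19 × 0.02 = 1.38.
- Total: 932 × 1.38 ÷ 0.75 = 1,714.9, against 1,716 stated (a rounding difference).
- Smallest significant difference, solving d = 1.96 √(2p̄(1 − p̄)/n) with a 25% control rate and n = 466: 5.35 points, in line with the stated 5.4.

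**What the forecast gives.**
- 2 years × 2 terms = 4 terms; (200 + 50) × 4 = 1,000. This is a floor, because the text says more than 200. 1,000 ÷ 1,716 = 58%.
- Needed for 1,716: 1,716 ÷ 4 = 429 per term, of whom 429 − 50 = 379 would be contacted students.
- Needed for 80% power at 1 year with 10% loss: 932 × 1.38 ÷ 0.90 = about 1,430, or 357 per term, of whom about 307 would be contacted students.

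**Other readings of the forecast.** Counting the 50 only once gives 4 × 200 + 50 = 850. A per-site reading would give 3 × 1,000 = 3,000, but the text says the figure is the total from all three sites. Neither gives 1,716.

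**Power for 25% versus 17.5%, 10% loss at 1 year.**

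| Enrolled | Design effect | n per arm, adjusted | Power |
|---|---|---|---|
| 1,716 | 1.38 | 559.6 | 86.7% |
| 1,430 | 1.38 | 466.3 | 80.0% |
| 1,200 | 1.38 | 391.3 | 72.8% |
| 1,000 | 1.38 | 326.1 | 64.9% |
| 1,000 | 1.19 | 378.2 | 71.3% |
| 1,000 | 1.00 | 450.0 | 78.6% |

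The 1.19 row allows for smaller groups at lower enrolment. It assumes four programs per site per term, so 4 × 3 × 4 = 48 program groups. Then 500 ÷ 48 is about 10 women per group, and 1 + 9 × 0.02 is about 1.19 (1.18 for exactly 10).

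**Other design figures at 1,000 women, 10% loss, 25% control rate.**
- Difference detectable with 80% power: 8.3 points (design effect 1.19) to 8.9 points (1.38), against 7.5 planned.
- Smallest significant difference: 5.9 points (1.19) to 6.3 points (1.38), against 5.4 stated.

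**The case against.** Several points on the other side are fair.

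- **The forecast is a lower bound.** This stands, so 1,000 is a floor and not a prediction. But 379 contacted students per term, or even 307, is not a natural reading of more than 200, and exceeding the floor by a fifth (1,200 women) still gives only 73% with the planned design effect.
- **The sample-size section is correct on its own terms.** This stands. Its power statement is conditional on 1,716 women, and that number leaves a margin for the 1-year outcome because it allows for 25% loss.
- **The planning ICC is conservative.** The pilot estimate was −0.02 and the plan uses +0.02. With no clustering the shortfall at 1,000 women nearly disappears (79%). The plan nevertheless chose +0.02 as its basis, and its stated power should be judged on that basis.
- **The forecast may be the slip.** On the assumed 48 groups, 1,716 women means 858 ÷ 48 = 17.9 per program group, close to the planned 20, whereas 1,000 means about 10. This suggests that delivery was scaled to the larger number, but the 48 is an assumption and does not settle the matter.

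A reader might also take the Trial status section as proof of a shortfall: "Currently, 918 women have been enrolled into the on-going trial". It is not. The count is undated, enrolment is described as ongoing, and the number of terms behind it is not given. Nor should the two-year loss be applied to the forecast number to show still lower power, since the primary comparison is at 1 year.

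**Conclusion.** The point holds as an unreconciled contradiction between the recruitment forecast and the enrolment target. The forecast floor is 58% of 1,716 and about 70% of the 1,430 needed for 80% power at 1 year. If only that number enrols, 1-year power is about 65% to 71% on the planned ICC, against the stated 80%. This rests on four recruiting terms, 10% loss, the planned event rates, and for the upper figure the assumed 48 groups.

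It would be tempting to conclude that the trial will be underpowered, or that the 80% statement is wrong. The article supports neither: 80% follows correctly from 1,716, and nothing shows which of the two figures is misstated. The estimand, randomization and analysis are unaffected. The passages should be fixed, but the design is not invalidated.

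**What to change.** Reconcile the Recruitment and Sample size considerations sections in one of two ways.

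1. If the forecast or the recruitment period is the misstated figure, correct it so that it leads to 1,716, and restrict the achievability statement to a rate that pilot experience supports.
2. If the forecast is right, state the enrolment that the recruitment plan supports, with the 1-year power for 25% versus 17.5%, the difference detectable with 80% power and the smallest significant difference. Use a group size in the design effect that is consistent with that enrolment.

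In either case, say that the 25% loss allowance relates to two years and give the 1-year power separately.

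The cost is a wording change and a short recalculation. Under the second option the stated power becomes less favourable. Extra recruitment effort arises only if the sponsor chooses to extend enrolment to reach the target.
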